### Randomization

An independent statistician will generate the random sequence by the central block randomization method using IBM SPSS Statistics, version 21.0 (International Business Machines Corporation, China). Eligible patients will be assigned randomly into the disease-affected meridians (DAM) group, non-affected meridians (NAM) group, and sham acupuncture (SA) in a 1:1:1 ratio. An independent researcher in charge of informing assignment will implement the allocation schedule through a centralized telephone randomization procedure. To ensure the allocation concealment, acupuncturists will make a call to ask for the information of assignment before the first treatment. The independent researcher will send messages containing allocation details immediately. Before randomization, trial information will be provided to each eligible patient. Researchers (doctors) will get written informed consent from eligible patients who are willing to participate.

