### Outcomes

The primary outcome is defined as the change of leg pain intensity on VAS from baseline to week 4 measuring pain over the prior 24 h. The VAS presents as a 0–100 mm ruler with 0 representing no pain and 100 representing unbearable pain. The specific score will be determined by the distance from 0 to the patient’s mark.

Secondary outcomes include VAS for leg pain and back pain at other time points, Oswestry Disability Index (ODI) [22], the Sciatica Frequency and Bothersomeness Index (SFBI) [23], 36-item Short Form Health Survey (SF-36) [24], straight leg raise test [25], painDETECT questionnaire [26], global perceived recovery on 7-point Likert self-rating scale [27], the Credibility/Expectancy Questionnaire [28], blinding assessment and medicine use. The ODI plays a role in giving a subjective percentage score of function level for patients with low back pain through examining perceived disability in 10 activities of daily living. The SFBI measures the frequency and symptom severity with scores ranging from 0 to 24 respectively. SF-36 is used to assess the quality of life on eight aspects including physical functioning, bodily pain, role limitations due to physical health problems, personal or emotional problems, emotional well-being, social functioning, energy/fatigue, general health perceptions, and a single item that indicates perceived change in health. PainDETECT questionnaire is used to discern the variation of neuropathic pain as one common method. A 7-point Likert self-rating scale is used to assess the recovery compared to the onset with options from “completely recovered” to “worse than ever.” The Credibility/Expectancy Questionnaire is capable to assess the credibility and expectancy of patients. Maintenance of blinding will be determined by asking patients to report the group which they believe they had been assigned to. Categories and frequency of medicines use during the trial will be recorded in detail. Detailed arrangements of every outcome are shown in Table 4.

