### Sample size

As a pilot study, we determine to use a convenience sample instead of a sample size calculation. Ninety patients will be enrolled in this trial, 30 in each group. The data of this pilot trial will be applied to facilitate the calculation of the sample size for a further RCT.

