### Statistical analysis

Continuous variables will be described by means and standard deviations or 95% confidence intervals when following a normal distribution. If not, the data will be shown by medians and interquartile ranges. Categorical variables will be described by frequencies and percentages.

All data will be analyzed following the intention-to-treat principle primarily. A per-protocol analysis will be used for primary outcome as sensitivity analysis covering patients who complete at least 10 treatment sessions without obvious violation. Analysis of variance (ANOVA), Kruskal-Wallis H test, or chi-square test will be used to compare the equilibrium between three groups at baseline. As for outcomes, one-way repeated measures ANOVA or Kruskal-Wallis H test will be applied for continuous variables and chi-square tests or Fisher’s exact test will be used for categorical variables as appropriate. Data analyses will be performed using IBM SPSS21.0 with the statistical significance of two-tailed *P* < 0.05 as exploratory.

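### The week-4 change in leg-pain VAS is compared with no baseline covariate, which usually costs some precision and leaves part of any chance baseline difference in the estimate

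*Protocol article*

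**What the plan says.** The Outcomes section of the protocol article states: "The primary outcome is defined as the change of leg pain intensity on VAS from baseline to week 4". The Statistical analysis section then names the outcome tests: "As for outcomes, one-way repeated measures ANOVA or Kruskal-Wallis H test will be applied for continuous variables". Neither is given a covariate, and no section of the article mentions ANCOVA or adjustment for baseline.

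Baseline data appear in one other place in the analysis section, where ANOVA, Kruskal-Wallis or chi-square tests "will be used to compare the equilibrium between three groups at baseline". No consequence is attached to the result.

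The Sample size section fixes 30 patients per arm without a power calculation ("we determine to use a convenience sample instead of a sample size calculation") and says the data will feed the sample size of a later trial. Significance is judged "with the statistical significance of two-tailed *P* < 0.05 as exploratory". Baseline leg-pain VAS is available for every patient, because 40 mm or more is an entry criterion and the change score starts from it.

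**The concern.** Subtracting baseline fixes the slope of week-4 VAS on baseline VAS at 1. For a noisy pain score the true slope is usually below 1, so subtraction over-corrects: an arm that happens to start higher shows a larger fall through regression to the mean alone. ANCOVA estimates the slope from the data instead.

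The named tests do not do this. A group-by-time repeated measures ANOVA on baseline and week 4 is equivalent to comparing mean change scores, and Kruskal-Wallis takes no covariate. A significance test of baseline balance does not alter the outcome estimate, whichever way it falls.

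Two things are at stake: the precision of the between-arm differences with 30 per arm, and the SD carried into the planning of the full trial. Where adjustment gains precision, the SD of change would make that trial larger than an adjusted analysis needs.

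**Working it through.** **Plan's own figure.** There is no power or precision calculation to reproduce. The only arithmetic is 3 × 30 = 90.

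**Inputs.** From the article: n = 30 per arm, the change-score outcome, and the 40 mm entry cut. Assumed, because the article gives none: baseline SD s0, week-4 SD s1, and their correlation ρ.

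**Formulas.**
- Change-score variance per patient: s0² + s1² − 2ρ·s0·s1
- ANCOVA residual variance: s1²(1 − ρ²)
- Slope of week 4 on baseline: b = ρ·s1/s0
- 95% range of the chance baseline difference between two arms: ±1.96·s0·√(2/30)
- Part of it left in the change-score contrast: (1 − b) times that difference, with reversed sign when b < 1

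**Precision, equal SDs.** The variance ratio ANCOVA/change reduces to (1 − ρ²)/[2(1 − ρ)] = (1 + ρ)/2.

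| ρ | Ratio | Change-score n per arm to match ANCOVA at 30: 30 × 2/(1 + ρ) |
|---|---|---|
| 0.3 | 0.65 | 46 |
| 0.5 | 0.75 | 40 |
| 0.7 | 0.85 | 35 |

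A simulation of three arms of 30 (SD 20 mm, 3,000 replicates, no centre effect) gave standard errors of 6.18 v 5.00, 5.22 v 4.53 and 4.03 v 3.71 mm for change v ANCOVA. Squaring the ratios gives 0.65, 0.75 and 0.85, which agrees with the formula.

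**Precision, narrower baseline.** The 40 mm entry cut may make s0 smaller than s1. With s1 = 22 mm:

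| s0 (mm) | ρ | ANCOVA variance | Change variance | Ratio |
|---|---|---|---|---|
| 18 | 0.3 | 484 × 0.91 = 440.4 | 324 + 484 − 237.6 = 570.4 | 0.77 |
| 18 | 0.5 | 484 × 0.75 = 363 | 324 + 484 − 396 = 412 | 0.88 |
| 15 | 0.3 | 440.4 | 225 + 484 − 198 = 511 | 0.86 |
| 15 | 0.5 | 363 | 225 + 484 − 330 = 379 | 0.96 |
| 12 | 0.3 | 440.4 | 144 + 484 − 158.4 = 469.6 | 0.94 |
| 12 | 0.5 | 363 | 144 + 484 − 264 = 364 | 1.00 |

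In the last row b = 0.5 × 22/12 = 0.92, so subtraction is already close to the best adjustment and nothing is gained.

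**Chance imbalance.** With s0 = 15 mm the 95% range is 1.96 × 15 × √(2/30) = ±7.6 mm. With s1 = 22 mm:
- ρ = 0.5: b = 0.5 × 22/15 = 0.73, leaving 0.27 × 7.6 = ±2.0 mm
- ρ = 0.3: b = 0.3 × 22/15 = 0.44, leaving 0.56 × 7.6 = ±4.3 mm

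**Power for one pair of arms.** This takes an assumed 15 mm difference at two-sided 0.05.
- SD 20 mm at both times, ρ = 0.5: 82% (change) v 91% (ANCOVA)
- SD 15 and 22 mm, ρ = 0.5: 84% v 85%
- SD 15 and 22 mm, ρ = 0.3: 72% v 78%

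**Centre term alone.** With six centres and no stratification, the approximate variance ratio of adjusted to unadjusted is (1 − ICC)(1 + 5/81): 1.06 at ICC 0, 1.01 at 0.05, 0.96 at 0.10 and 0.90 at 0.15. It breaks even at an ICC of roughly 0.06, and the article gives no ICC.

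**The case against.** The strongest reply is that this is an exploratory pilot with a convenience sample, so no power target can be missed. The statistical analysis plan is not shown, and covariates are often set there. The adjusted residual SD can be computed from the same data whatever test is reported, and planning from the change SD would only make the next trial larger. All of that limits the consequence, and it stands. It does not remove the point: the article names its tests, and as named they are unadjusted.

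A reader might infer more than the article supports:
- That baseline is ignored, or that imbalance passes in full into the result. It does not. Baseline VAS is subtracted to form the outcome, so only the (1 − slope) share remains.
- That the comparison is biased. Randomisation keeps it unbiased on average. The leftover share is an error conditional on the imbalance that happened to occur.
- That adjustment brings a large gain in power. The gain from 82% to 91% needs equal SDs, and with a narrower baseline SD it can shrink to about one percentage point or vanish.
- That leaving out centre also loses precision. This is not shown: at a low ICC a centre term alone costs up to about 6% in variance. The Randomization section says only "An independent statistician will generate the random sequence by the central block randomization method". It states no strata, but a condensed article's silence does not establish that there were none. Any claim about sparse centre-by-arm cells would rest on assumed block and centre sizes.

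**Conclusion.** The point holds as one of efficiency, not validity. The primary comparison is a stated unadjusted change-score analysis, and the balance tests do not repair it. Adjusting for baseline VAS is a specific improvement that should be made.

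Its size cannot be fixed from the article. The variance ratio is 0.65 to 0.85 with equal SDs and ρ of 0.3 to 0.7, and 0.77 to 1.00 with a baseline SD of 12 to 18 mm against 22 mm at week 4 and ρ of 0.3 to 0.5. The share of chance imbalance left in the contrast has a 95% range of about ±2.0 to ±4.3 mm at SDs of 15 and 22 mm and ρ of 0.5 to 0.3. All SDs and correlations are assumptions. In large samples ANCOVA is never less precise than the change score, but the gain may be close to nil. No precision gain from a centre term should be claimed.

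**What to change.** Analyse week-4 leg-pain VAS (or its change, which gives the same treatment contrast once baseline is in the model) by ANCOVA or a mixed model, with arm as a factor and baseline VAS as a continuous covariate. Report adjusted mean differences between arms with 95% CIs, and report the adjusted residual SD for planning the full trial. Keep the baseline table descriptive and drop the balance tests.

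Centre may be added as a factor, and certainly should be if randomisation was stratified by it. State which was the case.

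The cost is one degree of freedom out of about 87 (90 patients less three arm means) and a change of analysis wording, best settled before unblinded results are seen. The optional centre factor would take five more. No new data and no design change are needed.

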**Methods:**

This is a multicenter, three-arm, patient-assessor-blinded randomized controlled pilot trial. Ninety patients will be assigned randomly into 3 groups including disease-affected meridians (DAM) group, non-affected meridians (NAM) group, and sham acupuncture (SA) group in a 1:1:1 ratio. The trial involves a 4-week treatment along with follow-up for 22 weeks. The primary outcome is the change of leg pain intensity measured by the visual analogue scale (VAS) from baseline to week 4 after randomization. Secondary outcomes include functional status, back pain intensity, and quality of life. Adverse events will also be recorded.

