## Background

Sciatica is characterized by radiating leg pain along the course of the sciatic nerve sometimes accompanied by back pain and neurological deficits [1]. The prevalence ranges from 1.2 to 43% globally based on controversial definitions [2]. Lumbar disc herniation is the leading cause of 85% of patients with sciatica [3]. Sciatica affects daily life and productivity and consumes more health resources when compared to low back pain [4].

Conservative treatments are the first-line options for sciatica [5, 6]. Medicine and epidural steroid injection are commonly used although long-term benefits are uncertain and side effects (e.g., headache and dizziness) or complications (e.g., epidural hematoma) occur sometimes [7–9]. Most pain and related disabilities could resolve in weeks [5], but up to 30% of patients were reported with pain lasting for 1 year or longer [10]. Therefore, long-term effective and safe conservative treatments might be potential solutions.

Acupuncture has been widely used for pain diseases. Meta-analysis indicated that acupuncture had a persistent effect on 4 chronic pains which decreased only 15% after 1 year [11]. However, high-quality evidence remains scarce for acupuncture treating sciatica [12, 13]. Acupoints play a key role in treatment that different acupoint selecting strategies could generate discrepant effects [14, 15]. To optimize acupuncture strategy for sciatica, this pilot study will evaluate feasibility and efficacy of acupuncture with different acupoint selecting methods. The hypothesis is that acupuncture on disease-affected meridians might have better effects. Reliable data will be used to develop a better design including sample size calculation for a further randomized controlled trial (RCT).

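### The parametric test named for continuous outcomes, one-way repeated measures ANOVA, has time as its only factor and so does not compare the three arms on week-4 leg-pain change

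*Protocol article*

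**What the plan says.** The Outcomes section gives one number per patient as the primary outcome: "The primary outcome is defined as the change of leg pain intensity on VAS from baseline to week 4". The trial has three parallel arms, the DAM group plus the "non-affected meridians (NAM) group, and sham acupuncture (SA) group in a 1:1:1 ratio" (Abstract, Methods), and the Background states a between-arm hypothesis: "The hypothesis is that acupuncture on disease-affected meridians might have better effects".

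The Statistical analysis section handles baseline and outcomes in separate sentences. ANOVA, Kruskal-Wallis or chi-square "will be used to compare the equilibrium between three groups at baseline". For outcomes, "one-way repeated measures ANOVA or Kruskal-Wallis H test will be applied for continuous variables", with chi-square or Fisher's exact test for categorical variables. The outcome sentence names no arm factor, no arm-by-time term and no week-4 contrast.

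The Sample size section says "Ninety patients will be enrolled in this trial, 30 in each group" and "we determine to use a convenience sample instead of a sample size calculation". Testing is "with the statistical significance of two-tailed *P* < 0.05 as exploratory".

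**The concern.** In standard usage a one-way repeated measures ANOVA has a single within-patient factor, here visit. Its null hypothesis is that mean VAS is the same at every visit. Treatment arm does not appear in it. The primary outcome is already a single change score per patient, so no repeated factor is left to analyse, and the question is whether that score differs between arms.

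The mismatch matters because improvement over time is expected whatever the treatment does. The Background expects most pain to settle within weeks, and entry requires leg-pain VAS of at least 40 mm, so regression to the mean will lower later scores. A time-only test is therefore likely to be significant even if the arms do not differ.

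The two tests offered are also not counterparts. Kruskal-Wallis compares independent groups; the rank version of one-way repeated measures ANOVA is the Friedman test. If the choice depends on the distribution of the data, that choice also switches the hypothesis.

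**Working it through.** The plan has no power or sample-size figure to reproduce; 3 × 30 = 90 agrees with the stated total. The check is which hypothesis each test responds to.

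**Inputs from the article.** Three arms of 30; VAS 0–100 mm; change from baseline to week 4; two-sided 0.05.

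**Assumed, because the article gives no values.** SD 20 mm at each visit (range 15 to 25); within-patient correlation 0.5; baseline mean 60 mm.

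**Step 1: the test as named, against a between-arm test.** Simulation, 4,000 runs per scenario, two visits, proportion of runs rejecting at SD 20:

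| True improvement by arm (mm) | One-way repeated measures (time), 90 pooled | ANOVA of change between arms | Kruskal-Wallis on change |
|---|---|---|---|
| 20 / 20 / 20 | 100% | 5.0% | 4.7% |
| 10 / 10 / 10 | 99.7% | 4.5% | 4.3% |
| 30 / 20 / 10 | 100% | 93.1% | 92.2% |
| +15 / 0 / −15 | 2.1% | 99.9% | 99.9% |

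Rows 1 and 3 show the point: the time test gives the same answer whether or not the arms differ. Row 4 is an artificial case in which the arms differ but the pooled mean does not move; over SD 15 to 25 the time test rejects in 1.0% to 2.6% of runs.

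The time test could instead be run inside one arm of 30. With a 15 mm mean improvement, the noncentrality is 15/(SD/√30). An SD of change of 20 mm gives 4.11 and rejection probability 0.978; 25 mm gives 3.29 and 0.888. The article does not plan within-arm tests, so this only illustrates the point.

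**Step 2: the mixed-design reading, with arm as between-patient factor.** The visit schedule is in a table that is not reproduced in the text, so six visits are assumed, with DAM better by 0, 5, 15, 10, 6 and 3 mm and NAM equal to SA. Correlation is exchangeable. When one of three arms differs by d, the noncentrality is λ = n × (2/3) × d² / variance = 20 d² / variance.

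- Arm main effect. Mean d = 39/6 = 6.5. Variance of a patient's mean = 400 × (0.5 + 0.5/6) = 233.3. λ = 20 × 42.25 / 233.3 = 3.62; F(2, 87); power 0.37.
- Arm-by-time over all six visits. Σ(d − 6.5)² = 395 − 253.5 = 141.5. Error variance = 400 × 0.5 = 200. λ = 20 × 141.5 / 200 = 14.15; F(10, 435); power 0.72.
- Arm-by-time over baseline and week 4, which is the same test as ANOVA on change. d = 15; variance = 2 × 400 × 0.5 = 400. λ = 11.25; F(2, 87); power 0.85.
- ANCOVA at week 4. Variance = 400 × (1 − 0.25) = 300. λ = 15; F(2, 86); power 0.94.

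λ scales with (20/SD)². At SD 15 the four powers, in the same order, are 0.60, 0.95, 0.98 and 0.997; at SD 25 they are 0.25, 0.48, 0.65 and 0.78. The order is the same at all three SDs.

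**The case against.** The best defence is that this is loose terminology. Kruskal-Wallis stands in the same sentence, the categorical tests are ordinarily between-group tests, the preceding sentence compares three groups, and the hypothesis is comparative. One-way may simply mean one between-patient factor, arm, measured repeatedly. That is plausible, and it means the Kruskal-Wallis branch is outside the criticism. It does not rescue the parametric branch as written, because the name chosen denotes a different test. This is a named rule that does not fit the outcome, not detail left to an analysis plan.

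A reader might infer that the plan fails even on the mixed-design reading. The article does not support that. Over baseline and week 4, the arm-by-time term is identical to ANOVA on the change score and is valid. The low power of 0.37 belongs to the arm main effect alone, which averages in baseline and follow-up visits, and it rests on an assumed visit schedule and effect path.

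A reader might also infer that the trial's conclusions are undermined. The sample is one of convenience, no power is claimed and the P values are declared exploratory. The stated use is to plan a larger trial, and means and SDs are to be reported in any case. This part of the objection stands and lowers the weight of the point.

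**Conclusion.** Wrong as written, moderate severity, and limited to the parametric option. One-way repeated measures ANOVA, as named, tests change over visits and carries no comparison of DAM, NAM and SA. That it ignores arm follows from the definition of the test. How often it would reject depends on the assumed improvement, SD and correlation; for equal improvements of 10 to 20 mm at SD 20 it is practically certain to reject. Pairing it with Kruskal-Wallis leaves a distribution check to decide which hypothesis is tested. If a mixed design was intended, the remaining gap is that the term bearing on the primary outcome is not identified: the week-4 interaction would serve and the arm main effect would not.

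**What to change.** Replace the outcome sentence with a between-arm comparison. For example: the primary analysis compares leg-pain VAS at week 4 between the three arms, adjusted for baseline VAS, by ANCOVA or by a mixed model with arm, visit, arm-by-visit and baseline VAS from which the week-4 contrast is reported; the rank alternative is Kruskal-Wallis on the baseline-to-week-4 change; other visits are secondary.

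An unadjusted ANOVA on the change score would also remove the error. Baseline adjustment is preferred for precision (0.94 against 0.85 under the assumptions above).

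The cost is one sentence, with the same SPSS version and no new data. The article expects the study to finish by the end of March 2021, and the change should be made and dated before unblinding.

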**Discussion:**

The results will inspire the optimal acupuncture strategy for sciatica and help establish a better design as well as power calculation for a full-scale study.

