## Discussion

Acupuncture might be a potential therapy for sciatica while methodological issues (e.g., lack of random sequence generation, allocation concealment, and blinding) appear frequently in previous studies. Two recent trials provided restricted evidence in favor of acupuncture but both were conducted in a single center with small sample sizes [29, 30]. Generalization of these study results might be limited. This pilot study will be conducted in 6 centers and will develop a full-scale study in order to address the issues.

The mechanism of sciatica may relate to the distortion of the nerve roots and effect of local inflammatory cytokines [1]. Acupuncture is known to exert an analgesic effect through inhibiting cytokine production and activate sympathetic nerve fibers to increase endogenous opioids [31, 32]. It may normalize default mode network activity and modulation of descending pain processing that help treat sciatica [33].

According to the Traditional Chinese Medicine theory, sciatica belongs to disorders of gallbladder meridian and bladder meridian. Acupuncturists tend to choose acupoints on disease-affected meridians in clinical practice which is expected to produce better effect. In our study, acupoints in the DAM group are all attached to the two affected meridians while those in the NAM group are on other meridians less related to sciatica. The comparative results will inspire the optimal acupuncture strategy for sciatica.

The feasibility and efficacy of acupuncture for sciatica will be evaluated in this study. Other strengths involve that it is a multicenter study designed following the Good Clinical Practice guideline [34]. Acupoints are selected based on literature and practical experiences from experts. Our limitations include that we use a subjective primary outcome, while VAS is the commonest method for measuring pain. Based on practical conditions, acupuncturists could not be blinded in this trial but communications will be limited to minimize the impact. Outcomes of this pilot study will be used as evidence for a further RCT subsequently.

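### The stated outcome tests are at best three-group omnibus tests, which cannot show whether DAM is better and do not give the between-arm differences the later RCT needs

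*Protocol article*

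**What the plan says.** The Background of the protocol article gives a directional hypothesis about one arm: "The hypothesis is that acupuncture on disease-affected meridians might have better effects". It names no comparator. The abstract says "The results will inspire the optimal acupuncture strategy for sciatica". The main Discussion contrasts the DAM points with the NAM points and concludes "The comparative results will inspire the optimal acupuncture strategy for sciatica". It also says that efficacy will be evaluated, and the sham arm is the natural reference for that.

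Under Randomization there are three arms: DAM, "non-affected meridians (NAM) group, and sham acupuncture (SA) in a 1:1:1 ratio". Under Sample size, "Ninety patients will be enrolled in this trial, 30 in each group". That section describes a convenience sample with no power calculation and gives the use of the data: "The data of this pilot trial will be applied to facilitate the calculation of the sample size for a further RCT".

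Under Statistical analysis, for outcomes, "one-way repeated measures ANOVA or Kruskal-Wallis H test will be applied for continuous variables", with chi-square or Fisher's exact tests for categorical variables. Significance is two-tailed P < 0.05, labelled exploratory. Variables are to be summarised by means with SDs or 95% CIs, or by medians with interquartile ranges. The section names no contrast between two arms and no between-arm difference.

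**The concern.** Two comparisons carry the article's conclusions: DAM against SA (does it work?) and DAM against NAM (does the choice of meridian matter?). The tests it names ask a different question, namely whether all three arms are the same. A significant answer does not say which arm differs or in which direction. It can arise when DAM is no better than NAM, or when NAM is the better arm.

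Two things are at stake. First, a significant three-group result could be read as support for the DAM hypothesis when it is not. Second, the pilot's main product is input to the sample size of the next trial. That requires a difference for a named pair of arms, with its uncertainty and an SD. An omnibus P-value provides none of these.

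**Working it through.** **Inputs from the article.** Three arms at 1:1:1; 30 per arm, 3 × 30 = 90 in total; two-sided 0.05; primary outcome the week-4 change in leg-pain VAS (0-100 mm). The sample was one of convenience, so there is no power figure to reproduce.

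**Assumed inputs.** The article gives no SD and no effect size. I take an SD of the change of 15, 20 or 25 mm and a true advantage of 15 mm, with normal data, equal variances and all 90 patients analysed.

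**Step 1: what the named test compares.** In a one-way repeated measures ANOVA the single factor is the repeated one, here time, so the literal test asks whether scores change over visits. A group comparison needs a between-patient factor as well. The named alternative, Kruskal-Wallis, does compare the three arms, as an omnibus test. I therefore use the charitable reading, a three-group one-way comparison of week-4 change.

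**Step 2: what the omnibus test can distinguish.** Power depends on the arm means only through λ = n Σ(μᵢ − μ̄)² / SD², with 2 and 87 df. The sum of squares, with means in the order DAM, NAM, SA, is:

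- only DAM better (15, 0, 0): mean 5; 10² + 5² + 5² = 150
- only NAM better (0, 15, 0): mean 5; 5² + 10² + 5² = 150
- DAM and NAM equally better (15, 15, 0): mean 10; 5² + 5² + 10² = 150

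All three give the same λ = 30 × 150 / SD² and hence the same power:

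| Assumed SD | λ | Omnibus power, all three patterns |
|---|---|---|
| 15 mm | 20.0 | 98% |
| 20 mm | 11.25 | 85% |
| 25 mm | 7.2 | 65% |

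The equality is algebraic and does not depend on the assumed SD or effect. As a check for Kruskal-Wallis, simulation with DAM and NAM equal and both better than SA by 0.5, 0.8 or 1.0 SD gave significance in 47%, 88% and 98% of trials. In those same simulations a direct DAM-NAM t-test rejected in about 5%, as it should when those arms do not differ.

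**Step 3: what named contrasts would give.** The 95% CI half-width for a difference between two arms is t(0.975, 87) × SD × √(2/30) = 1.988 × SD × 0.2582 = 0.513 × SD:

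- SD 15 mm: 7.7 mm
- SD 20 mm: 10.3 mm
- SD 25 mm: 12.8 mm

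**The case against.** The strongest reply is that this is a one-paragraph summary in a journal article. The full protocol (version 2.0) and any SAP are not shown, and post hoc comparisons and multiplicity rules are commonly left to them. That stands against one stronger reading: a reader might infer that the plan excludes pairwise comparisons, but the article does not say so. It does not remove the point, because the article does name its outcome tests, and those tests do not match its own hypothesis.

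The second reply is that the trial is an exploratory pilot. This also stands. The 0.05 level is labelled exploratory, the sample is one of convenience, and the conclusions are hedged. A reader might infer a failure of confirmatory error control, or that unadjusted pairwise testing would inflate the family-wise error. The article schedules no ungated pairwise tests. With three equal arms, pairwise tests made only after a significant omnibus ANOVA keep the family-wise error near 5% under normality and equal variances.

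Third, a reader might infer that the omnibus test is simply less powerful than a direct contrast. That depends on the assumed pattern of means, which the article does not give, so the point does not rest on it.

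Fourth, the pairwise differences can be derived from arm means and SDs. That is true where means and SDs are reported; medians with interquartile ranges would not give them so directly. Even then, which differences to stress would be settled after seeing the results.

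**Conclusion.** The point holds as a mismatch between question and analysis. The hypothesis is about DAM and the discussion is about choosing between strategies, while the named tests are at best omnibus. An omnibus P < 0.05 is exactly as likely when only DAM, only NAM, or both equally are better by the same amount: 98%, 85% or 65% for 15 mm at SD 15, 20 or 25 mm. It therefore neither supports the hypothesis nor supplies what the later RCT needs.

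The power and precision values rest on the assumed SDs, the assumed 15 mm effect and full follow-up; dropout would widen the intervals. At roughly 8 to 13 mm either side of each difference, the pilot can inform an estimate but gives weak grounds for ranking strategies. The consequence is limited to interpretation and planning. The documents do not support calling it an error-rate failure or a reason to change the sample size.

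**What to change.** In the Statistical analysis section:

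1. Name DAM-SA and DAM-NAM in week-4 leg-pain VAS change as the contrasts of interest, and report each as a mean difference with 95% CI. NAM-SA may be reported as well.
2. State that these contrasts are exploratory, and either that they are unadjusted or how multiplicity is handled.
3. Say that conclusions will not rest on the omnibus P-value alone. If a repeated measures model is kept, state that it has group as a factor and how the week-4 contrasts are taken from it.
4. Temper the statements about an optimal strategy to fit half-widths of about 8 to 13 mm.

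The cost is analysis wording and a more modest conclusion. Recruitment is already complete, but no further patients or data are needed. The wording should be fixed before the allocation is unblinded.
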